## Abstract

(1) Combining aerobic, coordination and cognitive training allows for more improved physical and cognitive performance than when performed separately. A Nordic walking (NW) and two cognitive-motor circuit training programs (CT-c and CT-fit) are compared. CT-c and CT-fit stimulate cognition differently: CT-c, is through conventional complex coordination training performed in single and dual-task conditions; CT-fit, incorporates it into complex goal-directed actions, implemented by fitness gaming technology (2) The aim is to determine whether CT-fit brings additional benefits to cognition compared to more traditional training. (3) Forty-five healthy independent living community dwellers participants (65–80 years) will be included after a general medical examination. The main exclusion criteria are signs of cognitive impairments (Mini–Mental State Examination < 26/30) and physical impairments. Pre and post-tests will be performed to assess: cognitive functions (Montreal Cognitive Assessment; Trail Making Test; Stroop task, working memory test, Rey Complex Figure copy task, Oral Trail Making Test, and dual-task); motor fitness (Bipedal and unipedal balance test, gait assessments, Time Up and Go, chair sit and reach test and four-square stepping test); and physical fitness (10 m incremental shuttle walking test, maximal handgrip force, Timed-Stands test). (4) Incorporating cognitive demands into complex, goal-directed actions using fitness gaming technology should be the best solution to optimize training benefits.

## 1. Introduction

Aging leads to significant declines in brain functions, physical and cognitive performance that are responsible for the loss of behavioral adaptability in many daily living tasks. Most of these alterations result from sedentary or insufficiently physically and cognitively engaging behaviors. Consequently, developing effective solutions to counteract and delay these alterations is a major challenge for aging research and society. It is now widely demonstrated that physical activity can contribute to achieving this objective. The benefits of aerobic exercise and muscular resistance training for brain and cognition (e.g., executive control, working memory, and memory functions) have been demonstrated in numerous studies, reviews, and meta-analyses [1,2,3,4,5,6]. Moreover, a recent study showed that combining aerobic and muscular resistance exercise is more effective and beneficial for cognition than the single isolated aerobic or muscular resistance training [7,8]. Recently, however, Diamond and Ling [9] challenged the systematic link between aerobic exercise and executive functions (EF). Their findings highlighted the importance of the qualitative aspects of the motor skills supporting training interventions, together with the quantitative aspects (intensity, duration, frequency of sessions) (see Pesce [10] for a convergent point of view). Specifically, they argued that the magnitude of benefits of aerobic training on cognition depends on the type of motor skill supporting the aerobic effort, that is, whether the physical activity requires a more or less cognition-demanding control of movement (e.g., whole-body or multi-limb coordination). Indeed, several studies reported a positive relationship between older adults’ motor fitness (measured by movement speed, balance, fine coordination, and flexibility) and cognitive performance [11,12]. Evidence of this relationship also comes from interventional studies showing that complex motor skill training improved cognitive performance [13,14]. In addition, a systematic review concluded that coordination training induces a greater improvement of cognitive functions, compared to aerobic or/and muscular resistance training [15]. In older adults, the effectiveness of complex motor skills training to improve cognitive functioning could be reinforced by cognitive-motor dedifferentiation [16,17], which is reflected by increased correlations among cognitive, sensory, and motor domains with age [18,19]. Cognitive-motor dedifferentiation has been confirmed by brain imaging studies. They showed larger activation of the prefrontal areas during motor tasks in older adults, which suggested that executive functions become more involved in complex movement control (e.g., interlimb coordination) compared to younger subjects [20,21]. Convergent evidence also suggested a strong link between age-related alteration of executive functions and deficits in gait, posture [22], and bimanual coordination [23]. According to this theoretical framework, it can be hypothesized that, in older adults, motor skills training involves more cognitive resources than in younger adults and could, therefore, be particularly appropriate to improve cognitive functions [24]. Consequently, it can also be hypothesized that combining cardiovascular (aerobic) and complex motor movement training should be a more effective way to improve cognitive functions [25,26]. This issue was addressed in a previous study [27] by comparing the effects of Nordic walking training (NW), mainly relying on aerobic exercise [28,29], and those of a circuit training program (CT) combining aerobic exercise and complex motor skills. While NW was expected to induce significant benefits on cognition via exercising cardio-respiratory capacities and muscular strength, CT was conceived to allow practicing complex motor skills in combination with aerobic exercise, and then, to capitalize on the coalition of their respective effects on cognition. Accordingly, it was predicted that combining aerobic exercise and complex motor skill training (i.e., during CT) would result in greater effects on cognitive functioning than the NW intervention. However, the results did not confirm this hypothesis, thereby suggesting that NW training was more cognitively demanding than hypothesized in most physiological studies, which considered Nordic walking as only a highly demanding aerobic activity. This could be due to the complex coordinated movements involved in stick manipulation and the constraints on balance control resulting from walking on uneven ground. In addition, in our previous study, motor exercises practiced during the CT were seemingly not optimally designed and progressively incremented in difficulty to impact cognition. Thus, the question emerged of whether increasing the cognitive demands of the motor exercises included in the CT would result in greater benefits to cognitive functions than NW. The present study addresses this issue by relying on the framework proposed by Herold and colleagues [30], who differentiated two types of simultaneous association of cognitive and motor exercise in motor-cognitive training, namely the “Thinking while moving” (TwM) and “Moving while thinking” (MwT) task conditions. TwM training consists of dual-task (DT) training, that is, conditions in which a cognitive task is added to the motor task as a distractor for the cognitive resources, as when walking straight on a line at a given speed to reach a location while counting backward. According to Herold and colleagues, in dual-task training, the cognitive task (i.e., counting backward) is not relevant to the goal-directed walking performance. Instead, it perturbs the performance by forcing the participants either to share their cognitive resources between the two tasks or, if unable to do, to give a priority to one of them or to switch quickly one to the other [31,32]. Nevertheless, DT training has been shown to improve cognitive functions, as well as performance in complex motor-cognitive tasks (e.g., walking in environments strewn with obstacles) [33,34]. Conversely, MwT training refers to situations in which the cognitive processes are incorporated into the motor task, so that they are a prerequisite for the success of the goal-directed motor task. This happens, for instance, when walking as fast as possible around a pre-defined space in order to pick up some numbered objects in a given order (memorized or discovered while walking) or when a decision must be made while moving to find a way or to switch from one movement pattern to another. Thus, in the MwT training conditions, optimal functioning of cognitive processes (visual search, memory, and spatial orientation) is inherently required to succeed in the motor task [30]. Herold and colleagues [30] hypothesized that MwT training could be more effective than other training conditions (i.e., aerobic alone or complex motor tasks performed either in single or dual-task condition) since there are closer to cognitive and motor requirements of real-life situations (see Raichlen and Alexander [35] for a similar point of view). Therefore, capitalizing on our previous study [27], the purpose of the present experiment is to compare the effects on physical and cognitive capacities of the NW training program and those of two different circuit training, based on TwM and MwT task conditions, respectively. In the circuit training based on TwM conditions (henceforth, CT-c), cognitive processes are loaded thanks to the inclusion of complex whole-body and interlimb coordinated movements performed in single or dual-task situations. In the circuit training based on MwT conditions (henceforth, CT-fit), the cognitive processes are directly incorporated into complex goal-directed motor tasks, thanks to the use of a fitness gaming technology (i.e., the Fitlight Trainer™; Fitlight Sports Corp., Canada). This technology is currently used in sports training [36] and rehabilitation to improve physical and cognitive skills (e.g., reaction time, perception-action capacities, agility, and coordination). To our best knowledge, until now, studies that compare these two types of training (or comparable fitness gaming technologies) in older adults are lacking.

### Aims and Hypotheses

The present experiment aims at comparing the effects on cognitive and motor functions of three types of training programs (NW, CT-c, and CT-fit), which differ in the nature of cognitive-motor exercises. It is hypothesized that, while all training would induce similar physical and motor fitness benefits, the CTs protocols would induce higher cognitive benefits than NW. Moreover, CT-fit should induce higher executive benefits than the two other training programs, thanks to the inclusion of cognitive stimulation through MwT conditions.

## 2. Materials and Methods

### 2.1. Study Design

The study is a monocentric randomized trial. Training interventions will be carried out at the “Stade Marseillais Université Club” (SMUC, Marseille, France) that is, a multisport club proposing programs of physical activity adapted to older adults. All subjects must give their informed consent for inclusion before they participate in the study. The study will be conducted in accordance with the Declaration of Helsinki, and the protocol has been approved by the French National Ethics Committee (CPP IDF10 no. 2019-A03263-54) (registered also on ClinicalTrials.gov ID: NCT04504643). Pre- and post-tests will be carried out before and after the training period to evaluate the cognitive, physical, and motor benefits of each program. An evaluation will be done at the Institute of Movement Science (ISM) (Marseille, France).

### 2.2. Recruitment

Participants will be recruited through an advertisement in the local newspaper. After contacting the project manager, either through phone calls or e-mails, volunteers to participate in the study will be screened for inclusion.

### 2.3. Study Population and Eligible Criteria

Participants are independent-living community dwellers aged between 65 and 80 years. General health status and lifestyle behaviors will be assessed via telephone. Primary exclusion criteria are: signs of cognitive impairment, reflected by a Mini-Mental State Examination (MMSE) score below 26/30 [37], inability to practice physical activity at moderate to vigorous intensity, uncontrolled psychiatric or cardiovascular affections, uncorrected hearing and/or a visual impairment, and psychotropic or bradicardizing medical treatments all assessed by medical evaluations and screenings. Participants will be examined for each criterion separately. Participants familiar with the Fitlight Trainer™ methods and or ranked highly active according to the International Physical Activity Questionnaire (IPAQ) [38] will also be excluded. The ability to practice a moderate to vigorous physical activity (i.e., 60–70% of maximal heart rate or HRmax) will be assessed by a medical examination and incremental exercise test on a cycle-ergometer [39] supervised by cardiologists at the sports medicine department of the local hospital of Saint Marguerite in Marseille. The termination criterion of the incremental cycling test is fixed at 85% of the estimated HRmax (220-age). Electrocardiogram will be recorded during exercise. HR will be measured at rest, during the effort, and 3 min post-exercise test. Initial mechanical power will be set at 30 W for 1 min and then the workload will increase each minute by 15 W. Adaptation of the exercise protocol will be considered by medical doctors for participants reporting previous cardiovascular problems (e.g., 30 W/10 W/1 min; 10 W/10 W/1 min). Complete inclusion and exclusion criteria are listed in Table 1.

### 2.4. Randomization

A computer-generated, random sequence of permuted blocks (block size = 3), will be created in order to assign the requested number (15) of screened participants to each group.

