### 2.5. Informed Consent

Information about the organization of the training programs (location, schedule, attendance, coaches, evaluations, etc.) will be presented to the eligible participants by the principal investigator. No information will be provided, however, about the research hypotheses. Then, participants will sign an informed consent form. Participants flows are presented in Figure 1.

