#### 2.6.1. Nordic Walking (NW)

NW sessions will be performed in a nature park, which offers pathways of different lengths and levels of difficulty. Walking sticks will be provided by the coach to participants. As in our previous study [27], the coach will progressively increase the level of difficulty over the 8 weeks, trying to individualize, as far as possible, the requested effort level while managing the whole group in the nature park. The participants will be following the coach, who shows the way and adapts the walking speed and difficulty.

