### 2.12. Sample Size

The sample size calculation was performed using G. Power 3.1.9.7 (Kiel, Germany) [59]. In order to detect relevant between groups differences and in the changes from pre- to post-intervention, we calculated a sample size sufficient to detect medium effect sizes. Therefore, f = 0.25, α = 0.05, *p* = 0.80, were chosen to favor clinically significant effect sizes. To test the main hypotheses of the present study, 42 participants, are required. In order to compensate for possible dropouts, 3 more participants will be included. The three groups are composed of 15 participants each.

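### A fixed block of 3 for three equal arms makes 15 of 45 allocations certain to anyone who knows the previous two, which permits selection if allocation is sequential and visible

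*Protocol article*

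**What the plan says.** Section 2.4 of the protocol article specifies a computer-generated "random sequence of permuted blocks (block size = 3"), used to "assign the requested number (15) of screened participants to each group". The block size is a single stated value. No stratification is described, and section 2.1 says "The study is a monocentric randomized trial", so there is one allocation stream.

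There are three arms: Nordic walking (NW), conventional circuit training (CT-c) and circuit training with light-based gaming (CT-fit). Section 2.12 gives their size: "The three groups are composed of 15 participants each".

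On recruitment, section 2.2 says: "After contacting the project manager, either through phone calls or e-mails, volunteers to participate in the study will be screened for inclusion". Section 2.5 says that information about how the programmes are organised "will be presented to the eligible participants by the principal investigator", after which consent is signed.

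The arms are easy to tell apart. Under 2.6.1, "NW sessions will be performed in a nature park". Section 2.6 gives NW its own coach and the two circuits another. Section 2.6.3 replaces the dual-task stations of CT-c with light-based stations in CT-fit.

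The Data Availability statement says that data collection had not yet happened, so the block size was in print before the results.

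**The concern.** A block as long as the number of arms is the most predictable permuted-block scheme available. After two assignments in a block the third is fixed, and after one the next is a choice between two arms. In an open trial at one site, someone who follows the assignments can work out where each block ends.

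The stake is allocation that is random on paper but open to influence in practice. A person who foresees the next assignment could delay, reorder or discourage a volunteer. Arms of 15 leave little room to average this out. For scale only, and as an assumption: if between 1 and 3 of the 15 participants in an arm differed by 1 SD because of such choices, the arm mean would move by 1/15 to 3/15 SD, that is 0.07 to 0.20 SD. Nothing in the article says that this would happen, or in which direction.

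**Working it through.** **Inputs.** Block size 3, fixed (2.4). Three arms (Aims and Hypotheses). 15 per arm, so 3 × 15 = 45 in total (2.12). One centre (2.1).

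**The plan's own figures.** 45 / 3 = 15 complete blocks, each with every arm once, gives 15 per arm, as stated. The required 42 in section 2.12 also reproduces: for a repeated-measures ANOVA group-by-time interaction with f = 0.25, α = 0.05, three groups and two time points, N = 42 gives power 0.803. This assumes a pre/post correlation of 0.5 and no sphericity correction, neither of which is stated. Block size does not enter this calculation.

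**Predictability with blocks of 3.** Assume the guesser knows the earlier assignments and the block boundaries. The best guess is right with probability:

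- position 1: 1/3
- position 2: 1/2
- position 3: 1

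Expected correct guesses = 15 × (1/3 + 1/2 + 1) = 15 × 1.8333 = 27.5 of 45, or 61%. Chance gives 45 × 1/3 = 15, or 33%. Certain allocations: 15 × 1 = 15 of 45. Allocations narrowed to two arms: another 15.

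**Alternatives.** Fixed blocks and the single list were enumerated exactly, with the guesser knowing the scheme. Varied sizes were simulated with 2,000 sequences and a guesser who knows the possible sizes but not their order.

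| Scheme | Certain allocations of 45 | Expected correct guesses of 45 |
|---|---|---|
| Fixed 3 (plan) | 15.0 | 27.5 (61%) |
| Fixed 6 | 9.0 | 25.2 (56%) |
| Fixed 9 | 6.4 | 23.9 (53%) |
| Random 3, 6 or 9 | about 1.7 | about 24.7 (55%) |
| One shuffled list, 15 per arm | 1.5 | 19.7 (44%) |

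The fixed-6 row is a per-block rate scaled to 45, since 45 / 6 is not a whole number.

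The simulation drew sizes independently with equal probability and cut the list at 45. A list built to end exactly at 45 is slightly more predictable near its end. Repeating the simulation with every ordering of sizes 3, 6 and 9 that sums to 45 equally likely gave about 2.0 certain allocations and 25.6 correct guesses. The varied-block figures are therefore approximate, but the conclusion is the same: varied sizes remove nearly all certain allocations and lower the overall guess rate only modestly.

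**From predictability to selection.** Two further facts are needed:

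1. Participants are allocated one after another while enrolment is open.
2. Those who screen or enrol learn earlier assignments.

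Section 2.2 describes screening, not the timing of assignment. Section 2.4 says that screened participants are assigned, not when or by whom. Figure 1, the participant flow, is not available in the text reviewed.

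**The case against.** A reader might infer that recruiters will see past assignments and steer volunteers into CT-fit, giving a bias toward the hypothesis that no analysis can remove. The article does not support that.

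- **Timing and access are not stated.** Screening people individually does not mean assigning them individually. Wording about assigning 15 screened participants to each group, and training run in groups and pairs, is compatible with batch assignment.
- **Recognisable arms are not the same as visible assignments.** Training is at the sports club and testing at the institute (2.1). Seeing who attends which programme helps a recruiter only if training starts while enrolment is still open.
- **Concealment may be covered elsewhere.** A journal article can leave the list-holder and the release procedure to the full protocol, so their absence is not a fault here.
- **Bias is not quantified.** The analysis uses pre- and post-tests (2.13), so a baseline imbalance would be visible and partly differenced out. Fitter starters may also gain less. Several entry criteria (MMSE cut-off, IPAQ category, supervised exercise test) limit discretion.

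These arguments stand, and they limit the point to a conditional risk. They do not rescue the block size, which is stated outright. If assignment is sequential, a block of 3 is the most predictable choice. If it is by batch, a single shuffled 15/15/15 list gives the same final balance and the small block adds little.

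It would also be too strong to say that varied sizes hide block ends completely: about 1.7 allocations remain certain to someone who knows the possible sizes.

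**Conclusion.** The point holds as a weakness in a stated design choice. With the fixed block of 3, 15 of 45 allocations are determined by the two before them, 15 more are narrowed to two arms, and best guessing reaches 61% against 33% by chance. These figures follow from the block size and arm count alone.

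The list opens the door to selection only if allocation is sequential and those who screen or enrol know earlier assignments. The article establishes neither, so this is an avoidable risk and not a demonstrated bias. Because the change is nearly free before enrolment, it is worth making.

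**What to change.** **Preferred:** obtain consent and complete pre-tests for each recruitment wave, or for the full cohort, and then assign everyone in it at once from a shuffled equal-allocation list. Those assigned are already enrolled, so foreknowledge has nothing to act on. State this order in section 2.4.

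**If allocation must be sequential:** replace the fixed block with randomly ordered blocks of 3, 6 and 9 summing to 45, with 15 per arm. Withhold the sizes from those who screen or enrol. The main gain is the loss of nearly all certain allocations, with a modest fall in the guess rate.

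**Cost:** regenerate one list and amend a sentence. Varied blocks allow a small temporary imbalance between arms during recruitment. The final 15 per arm and the sample size of 42, or 45 with the dropout allowance, are unchanged.

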### 2.5. Informed Consent

Information about the organization of the training programs (location, schedule, attendance, coaches, evaluations, etc.) will be presented to the eligible participants by the principal investigator. No information will be provided, however, about the research hypotheses. Then, participants will sign an informed consent form. Participants flows are presented in Figure 1.

### 2.6. Intervention Description

The three training programs are administered by two professional coaches, one for NW and one for the two circuit training interventions (CT-c & CT-fit). The three programs last 8 weeks, with 3 sessions of 1-h per week (24 h in total). For each intervention program, core training sessions will last 50 min, while the remaining 10 min are spent equally on the warm-up and cool-down. The heart rate of the participants of the three groups is recorded via a heart rate monitor provided to each of them before starting the training program and pre-set with their characteristics (gender, weight, height). The heart rate monitor allows controlling the intensity level of physical effort during the core session. During each session, participants are encouraged by coaches to maintain an intensity corresponding to 60–70% of HRmax. The heart rate monitor also allows ensuring that the mean heart rates reached during each session are roughly equivalent to the different training programs. In each session, at the end of the core session, just before the cool-down, participants will be asked to rate their effort using the Perceived BORG scale, ranging between 1 and 10 (with 1 representing absolutely no effort and 10 extreme maximal effort) [40].

